### Interventions

#### Personalised diet

The PD intervention involves individual dietary counselling by a dietitian/trained nutritionist/research scientist and daily consumption of PPF products (detailed description below). The intervention aims at achieving the following predefined nutritional targets: Daily consumption of 2 × 25 g PPF powders added to food/drinks.Daily energy intake of 25–30 kcal/kg body weight^(54)^.Daily protein intake of 1–1.2 g/kg body weight from food and PPF^(55)^.

These nutritional goals are based on previous research in older adults^(54,55)^. As recommended by expert consensus statements^(2)^, participants will be regularly monitored and nutritional targets will be adjusted according to each participant’s current nutritional status and co-morbidities requiring specific dietary strategies. One personalised dietary advice session (about 45 min) will be delivered in person at the start of the intervention, and two 35–45-min sessions via telephone (weeks 4 and 8). In addition, fortnightly compliance telephone calls will be conducted by a trained member of the research team. The personalised dietary advice will be based on the following assessments: (i) 3-d food diary (week before starting intervention, see below), (ii) nutritional assessment at baseline and (iii) two single 24-h dietary recalls via telephone (weeks 4 and 8).

As part of the nutritional counselling, participants will be provided with a ‘Hints and Tips’ booklet with suggestions, including recipes, on how to incorporate the PPF powders into their everyday foods/meals/snacks/beverages, preferably in meals, snacks and/or beverages that contain 6–7 g protein from other sources (e.g. 20–25 g meat, 40 g fish, one egg, glass of milk, 125 ml yogurt, 25 g cheese, 2 thick slices bread, 25 g almonds or Brazil nuts), to enhance circulating methionine, as methionine appearance was found to be limited following PPF consumption^(56)^. As a priority, participants will be instructed to include a full 25 g sachet of PPF powder at two meals where protein intake is identified as being low (e.g. breakfast and lunch), to optimise protein distribution^(20)^. Participants will only be advised to spread the two sachets across multiple eating occasions if they report significant difficulty with consuming a full PPF sachet at one meal.

Where needed, participants will also be provided with country-specific resources that provide simple advice on how to address poor appetite and meet energy requirements to support the participant achieving a daily dietary intake of 25–30 kcal/kg and 1–1·2 g protein/kg body weight., for example, Nutrition supports – HSE.ie^(57)^.

#### Description of plant protein fibre products

Initially six varieties of PPF blends from different plant sources were developed by Fraunhofer Institute for Process Engineering and Packaging (IVV) (Freising, Germany) as part of the APPETITE project^(49)^. The PPF blends were designed to provide equivalent leucine and closely matched branched chain and indispensable amino acids and align with optimal values described for older adults to promote muscle mass and strength^(58)^. Their acceptability in a food matrix (natural yogurt) and sensory properties were subsequently tested by older adults (> 65 years, *n* 25) at two trial centres (FAU, Germany and UCD, Ireland). The three blends with the greatest acceptability had mean (sd) Likert scale (0–9 point) scores of 5 (2), corresponding to ‘neither like nor dislike’, similar to acceptability of oral nutritional supplements in older adults reported in previous studies^(59)^.

These three PPF blends were subsequently investigated for circulating plasma amino acid appearance following ingestion of the products in older adults, with results reported elsewhere, including quantitatively measured amino acid composition of the blends^(56)^. Based on these findings, two blends (referred to as PPF A and PPF B) were selected for the RCT. PPF A consists of 54 % pea protein isolate, 17 % oat protein concentrate, 9 % almond protein concentrate and 20 % vegetable pea fibre, with a 25 g sachet providing 15·3 g protein and 3·6 g fibre. PPF B consists of 36 % pea protein isolate, 26 % soya protein isolate, 18 % rice protein isolate and 20 % vegetable pea fibre, with a 25 g sachet providing 17·1 g protein and 3·6 g fibre. The ingredients used for the PPF formulation are commercial protein ingredients resulting from dry and wet fractionation of plant raw materials. The fibre ingredient is a commercial product derived from pea kernels after protein extraction. The protein contents of the ingredients and the nutritional composition of the PPF are provided in more detail in the previous publication of de Marco Castro *et al.*
^(56)^ and in Appendix 4. Participants will be given the same quantity of each PPF and advised to consume one sachet of each type per d.

### Physical activity

The PA intervention involves group exercise classes in a supervised setting twice per week (with at least 48 h between training sessions) and home-based walking three times per week, following a similar format to previous multi-centre trials in community-dwelling older adults ^(54,60)^.

The group exercise class will begin with a warm-up including training on walking dynamics. This will be followed by approximately 3–4 balance exercises. Resistance exercise will then be conducted in line with guidelines for resistance exercise in older adults^(61)^. Upper and lower body exercises will be completed using adjustable weights across centres including the following exercises: wide leg squat, standing leg curl, hip flexion, knee extension, seated row, bicep curls, seated shoulder press, along with push-ups (against a wall). The exercise intensity will progressively increase so that all participants should be achieving an intensity of 15 to 16 on the Borg 6–20 rate of perceived exertion (RPE) scale^(62)^. Weights will be increased individually so that this intensity is maintained throughout the remainder of the programme. For each strength exercise, participants will be instructed to perform 8–12 repetitions (one set), rest for approximately 1 min and then perform subsequent sets. The sets and repetitions prescribed will progressively increase over the 12-week programme. For example, in week 1, participants will perform eight repetitions (one set) per exercise, rest for approximately 1 min and then perform a second set. As the participants progress, repetitions will increase from 8 to 10 to 12 and sets will increase from 2 to 3 sets per exercise.

For home-based walking, the goal is 60 min (3 × 20 min) of walking per week during the first 3 weeks, 90 min (3 × 30 min) per week for weeks 4–6 and finally 120 min (3 × 40 min) per week for weeks 7–12. The walking goals may be accumulated over the day until participants are able to achieve the continuous duration. Walking pace should be at a moderate intensity defined as an RPE of 13 on the Borg 6–20 scale^(62)^. For individuals who are very deconditioned, it is acceptable to exercise at an RPE < 11 in the initial 3 weeks until they become more comfortable with the exercise protocol.

#### Personalised diet and physical activity

Participants in the personalised diet and physical activity (PD + PA) group will undertake both PD and PA interventions combined. Participants will follow identical procedures to those described in the PD and PA interventions above.

#### Control

The control group will receive no intervention, and participants are instructed to maintain their usual diet and PA which is considered standard care for older adults with poor appetite across study centres. Participants will be provided with tailored nutritional and lifestyle information following study completion.

### Maximising and monitoring compliance with personalised diet and physical activity interventions

Adequate weekly compliance in the PD group is defined as self-reported consumption of at least ten of a possible fourteen PPF powder sachets in that week, similar to previous supplementation studies^(63)^. Participants will be asked to complete a daily log, ticking a box to indicate that they have consumed each powder sachet. In addition, participants will be asked to keep all empty sachets in a container provided by the research team at the baseline test visit, as an additional objective measure of compliance. This must be returned at the end of the study. Overall compliance is defined as adequate compliance for at least 9 weeks during the 12-week intervention (75 %).

During the fortnightly compliance telephone calls in the PD and PD + PA groups, compliance with the intervention will be encouraged and problems troubleshooted. For participants in the PD + PA group, this may instead be conducted in person before/after an exercise class, and for participants in the PA group it will be conducted in person before/after an exercise class to reduce participant burden.

Adequate compliance in PA groups is defined as completing a minimum of 75 % of group exercise sessions (i.e. a minimum of eighteen out of twenty-four sessions). Attendances will be recorded by the instructor at all supervised sessions. Home-based walking and all moderate to vigorous activity will be recorded in the compliance log. Compliance logs will be checked by trained researchers throughout the intervention at exercise sessions.

If participants do not adhere to the above interventions, they will be included in intention-to-treat analysis and excluded from per-protocol analysis.

### Data collection and study outcomes

Data will be collected on two separate test visits at baseline and two identical visits post-intervention (week 13) (Fig. 1). One visit consists primarily of assessment of physical characteristics and function, and the other visit consists of an appetite test meal challenge. Participants will be instructed to avoid strenuous exercise and alcohol in the 24 h before testing on both occasions. Participants will also be instructed to fast for at least 10 h overnight, prior to arrival at the laboratory, and to consume nothing other than water during this time. A small glass of water is advised upon waking on the morning of testing. Participants will be instructed to follow their normal medication routine, and any smokers that are eligible will be instructed to avoid smoking/vaping on the morning of testing. A standardised snack will be provided to participants prior to physical function testing. For post-intervention testing, identical procedures will be followed. A summary of the data collection variables/measures and time points of collection is shown in online Supplemental Appendix 5.

### Primary outcomes

#### Subjective appetite and ad libitum test meal energy intake

The joint primary outcomes are (i) postprandial composite appetite score (area under the curve from 0 to 180 min (AUC_0–180 min_)) derived from three 100 mm VAS (hunger, fullness and desire to eat) and (ii) energy intake (kilocalories (kcal)) from an *ad libitum* lunch test meal. Appetite ratings will be assessed at the following time points: fasting before (*t* –10 min) and after a standardised breakfast (see below) (0 min, 30 min, 60 min, 120 min, 180 min and post-lunch). This time frame represents a typical inter-meal interval during which time an oscillating pattern of hunger and fullness would be expected^(64,65)^. Composite appetite score is calculated as follows: (VAS hunger + VAS fullness (100-rating) + VAS desire to eat)/3. On either end of the VAS 100 mm line are opposing terms (i.e. ‘not at all’ and ‘extremely’). The trapezoid method will be used for the calculation of AUC. The *ad libitum* test meal will be served at 180 min and energy intake will be assessed.

The joint primary outcomes were selected to include a subjective and an objective measure of appetite, reflecting different processes of appetite control^(64)^. VAS have a history of widespread use and acceptance across many countries and laboratories, and according to consensus recommendations, they are easily used and translated and appear to be a valid, sensitive and unbiased measurement tool of appetite^(8)^. VAS have been validated for assessment of appetite, including in older adults^(66–68)^.

#### Test meals

The fixed breakfast meal consists of white bread toasted (88 kcal), butter (36 kcal), jam (24 kcal), orange juice (82 kcal) and strawberry yogurt (111 kcal), providing approximately 340 kcal overall, 57 g carbohydrate (66 % energy), 8 g fat (22 % energy) and 11 g protein (12 % energy) across all centres.

The *ad libitum* lunch test meal consists of a homogenous pasta-bake meal, identified as being acceptable to older adults across all centres. The key ingredients are pasta, tomato-based pasta sauce, cheese and olive oil, providing approximately 1900 kcal, 17 % energy protein, 54 % energy carbohydrate, 28 % energy fat (maximum 1 % energy deviation between centres). The meal is freshly prepared and provided in a large serving dish with utensils and a bowl into which participants help themselves. Participants are instructed that they have 30 min to help themselves to and eat as much as they wish until they feel comfortably full. Water intake is recorded and the amount of food consumed is determined by weighing the meal before and after consumption. Energy intake is calculated using the manufacturers’ energy values.

### Secondary outcomes

#### Anthropometric measurements and body composition

Height, weight and seated maximum calf circumference of the dominant leg will be measured in duplicate using a stadiometer, digital scale and flexible measuring tape, respectively. Body resistance at 50 kHz will be measured by bioelectrical impedance analysis (BIA) at all sites as follows: Germany: (Impedimed Imp SFB7, Impedimed Limited, Queensland, Australia), Ireland: Bodystat QuadScan 4000, Bodystat Ltd, UK; Italy: BIA 101 BIVA® PRO, Akern Systems, Firenze, Italy) in a fasted state. Appendicular skeletal muscle mass, fat mass and fat-free mass will be estimated using validated equations in older adults^(69,70)^. Fat mass and fat-free mass will additionally be assessed by air displacement plethysmography (BodPod, Cosmed, Italy) at one site (Ireland), and fat mass, fat-free mass and appendicular skeletal muscle mass by dual-energy X-ray absorptiometry at one site (Italy).

#### Simplified Nutritional Appetite Questionnaire

Appetite will also be assessed via SNAQ^(71)^, a self-administered questionnaire adapted from the Appetite, Hunger and Sensory Perception questionnaire^(72)^. The four-item SNAQ includes questions on appetite, fullness, taste and frequency of eating and has been shown to predict weight loss in community-dwelling older adults^(57)^. It will be completed at baseline during in-person screening and post-intervention on the test day assessing physical characteristics and function.

#### Fasting appetite ratings

Fasting appetite ratings for hunger, fullness and desire to eat will be assessed using 100 mm VAS prior to consumption of the fixed breakfast meal.

#### Palatability of test meals

Palatability of the breakfast and lunch meals will be assessed using six 100 mm VAS. Questions include how pleasant was the meal, how satisfying was the meal, how tasty was the meal, how filling was the meal, how sweet was the meal and how savoury was the meal. Each end of the VAS is anchored with the words ‘not at all’ and ‘extremely’.

#### Dietary intake

Energy, protein and fibre intake will be assessed using a 3-d non-weighed food diary administered at baseline (pre-intervention) and in the final week of the intervention or control period. Participants will be instructed orally and in written form to record all items of food and beverages consumed and provide details of the brand, estimated quantity and cooking methods used. Energy and nutrient intake will be calculated using national nutrient databases ^(73,74)^.

#### Cardiorespiratory fitness, physical function and strength

Cardiorespiratory fitness will be estimated using a usual-paced 400 m walk test^(75)^. Physical function will be assessed by Short Physical Performance Battery (SPPB) combining the assessment of balance, gait speed and repeated chair stands tests^(76)^. Individual test scores and overall score will be calculated. Leg strength of the dominant leg will be assessed as the maximum value from three trials using a seated leg extension dynamometer to determine maximal voluntary isometric contraction of the knee extensors. Handgrip strength will be assessed as the maximum value from three trials with a Jamar hydraulic grip strength dynamometer, with the participant in a seated position and arm rested on the table at a 90-degree angle using the dominant hand, unless contraindicated.

#### Physical activity

PA and sedentary behaviour (including steps and METs, time spent walking, sedentary time and sit to stand transitions per d) will be assessed by ActivPAL accelerometer (activPAL3^TM^ micro, or activPAL4; PAL Technologies Ltd). The participant will be provided with the accelerometer to wear on the midline of the thigh for 7 d at baseline prior to commencing the intervention and during week 12 of the intervention or control period. Participants will also complete the Physical Activity Scale for the Elderly (PASE) questionnaire^(77)^. The PASE questionnaire is a brief and easily scored survey designed specifically to assess PA duration, frequency and exertion over a 7-d period in individuals 65 years and older. At post-intervention, participants will be instructed to include activities undertaken as part of the intervention in their response.

#### Resting energy expenditure

Resting energy expenditure (kcal/d) will be assessed following an overnight fast in participants at one site (Ireland) using indirect calorimetry (Q-NRG, Cosmed).

#### Cognitive status, dietary restraint and depressive symptoms

Cognitive status will be assessed by Mini Mental State Examination (MMSE)^(78)^. Cognitive dietary restraint will be assessed using the cognitive dietary restraint subscale of the Three-Factor Eating Questionnaire (TFEQ)^(79)^. The subscale consists of six ‘true/false’ and Likert scale-type questions relating to cognitive dietary restraint from the original fifty-item questionnaire. Depressive symptoms will be assessed by Centre of Epidemiology Study – Depression (CES-D) questionnaire^(80)^.

#### Quality of life

Subjective rating of perceived Quality of Life will be assessed using the EuroQol (European Quality Of Life) questionnaire (EQ-5D-5L)^(81)^. This consists of self-assessed rating of health under five dimensions (Mobility, Self-Care, Usual Activity, Pain/Discomfort, Anxiety/Depression) and perceived overall health on a VAS (0–100) anchored with opposing statements (0= the worst health you can imagine; 100= the best health you can imagine).

#### Blood biochemical measures

A fasting venous blood sample will be collected from participants at all sites prior to consumption of the fixed breakfast meal at baseline and post-intervention. Serum, lithium heparin and EDTA aprotinin tubes will be collected, processed according to standardised protocols and samples stored in aliquots at –80°C until analysis. Biomarkers related to appetite including ghrelin, GLP-1, PYY, glucose, insulin and leptin will be analysed centrally at one site (Ireland), except for plasma samples which will be transferred to National Research Institute for Agriculture, Food and the Environment (INRAE), France, for metabolomic analysis.

Postprandial samples in response to the fixed breakfast meal will also be collected at one site (Ireland) at baseline and post-intervention. Along with fasting measures, appetite-related gut hormones (ghrelin, glucagon-like peptide-1 (GLP-1) and peptide YY (PYY) will be assessed at 30, 60, 120 and 180 min post-breakfast until the *ad libitum* lunch test meal is served at 180 min and analysed in Ireland. In addition, metabolomic analysis will be conducted at INRAE, France, on postprandial samples collected at the same time points. At each site, all samples will be analysed together upon completion of the trial.

#### Gut microbiome diversity and gut metabolomic profiles

Gut microbiome diversity and metabolomic profiles will be assessed from a faecal sample and faecal water collected at baseline and post-intervention from participants at two sites (Ireland and Germany). Samples will be stored at –80°C until being analysed centrally (Ireland) after completion of the trial. Gut microbiome diversity will be assessed using 16S rRNA sequencing.

#### Muscle motor unit behaviour and muscle signalling

Motor unit behaviour^(82)^ will be determined by high-density electromyography on the vastus lateralis muscle (OT Bioelettronica) at one site (Italy). The primary outcome variables extracted from high-density electromyography will be motor unit mean discharge rate (pps), including discharge rate at recruitment/plateau/de-recruitment, muscle fibre conduction velocity (m/s) and persistent inward currents.

Muscle signalling related to muscle plasticity, metabolism, denervation and capillarisation will also be determined from muscle biopsies, at baseline and post-intervention, from participants who consent at one site (Italy). Biopsies will be taken using MEDAX/BF14100-C0; Bio-Feather with coaxial 14 g 10 cm and subsequently stored at −80°C. Sample analysis will be performed after completion of the trial. The following parameters will then be measured in the sample using western blot with specific antibodies for total proteins or by their activated phosphorylated form: (1) markers of denervation (AChR; agrin/MuSK/Lrp4, NCAM, Myog); (2) markers of protein turnover (atrogin1, MURF1, LC3, BNIP3, Akt-dependent mTOR and FoxO); (3) markers of mitochondrial dynamics (OPA1, DRP1); and (4) markers of energy metabolism pathways (AMPK and PGC1alpha).

#### Acceptability of the trial

To determine acceptability and feasibility of the intervention and overall experience while enrolled in the study, a study-specific questionnaire designed similar to previous studies^(83)^ containing statements (e.g. *I was able to integrate the programme into everyday life*) and five-point Likert scale responses ranging from ‘*Strongly disagree’* to ‘*Strongly agree’* will be administered to participants on completion of the intervention. The questionnaire will also enable participant challenges and suggestions to be reported through open questions (e.g. *What helped you (or made it difficult) to follow through with the programme?*). In addition, for participants in the PD groups, feedback on the PPF products will be recorded at the end of the intervention and during the dietary recall telephone calls with open questions (e.g. *How did you integrate the PPF products into your diet?).*

### Adverse effects and events

Any adverse effects will be recorded as reported by participants during the trial, for example, during fortnightly telephone calls for PD groups, during PA classes or if a participant contacts the research team to report adverse effects or events at any time during the trial.

### Data management and statistical analysis plan

All data will be collected on questionnaires and record sheets in a de-identified manner using a participant ID number and stored securely according to General Data Protection Regulation (2018)^(84)^ at each site, with electronic data double-entry into a central electronic database stored and backed up at one site (Ireland). The trial coordinating centre Principal Investigators will have access to the full dataset across all sites. Study site Principal Investigators will have direct access to the dataset at their own site and will have access to data from other sites by request. Anonymised data will be made available to other researchers on reasonable request after the main trial manuscript is published.

There are no plans for interim study analysis. After completion of the study data collection, data will be checked and cleaned using descriptive statistics and data visualisation. Outcome data will first be analysed according to the intention-to-treat principle, using a random coefficients generalised linear mixed model for primary and secondary end points. The effects of time, the two interventions and their interaction (following the 2 × 2 factorial design of the trial) and sex will be included as fixed effects. Participant ID and study site will be included as random effects. Residuals will be tested for normality and transformation applied where required, or where the structure of the data is inherently non-normal. 95 % CI will be reported where applicable. Per-protocol analyses and mediation analyses will be conducted to examine to what extent compliance and potential mediating mechanisms explain the impact on the primary and secondary end points. For primary pre-planned contrasts, significance will be accepted as *P* < 0·05. Where groups of secondary outcomes are analysed, the significance level will be adjusted by Bonferroni correction according to the number of responses in the analysis. A correlation matrix will be constructed to assess relationships between outcome variables. Missing data will not be imputed in the primary analysis. Intention-to-treat analyses will be based on the *as-observed* population.

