### Study design

The trial is a multi-centre RCT aiming to recruit 180 community-dwelling older adults (about 60 per centre) in Nuremberg – Germany, Dublin – Ireland and Padua – Italy, all urban settings. Employing a 2 × 2 factorial parallel-group design, outcome measures will be assessed pre and post a 12-week intervention. Participants will be randomly allocated (1:1:1:1) by study centre and sex to one of four groups: Personalised diet (PD): daily consumption of two PPF products and dietary counselling over a 12-week period;PA: group exercise classes twice per week and home-based walking over a 12-week period;PD and PA: both interventions described above combined;Control: no intervention, usual diet and PA.

An overview of the timeline for participants is shown in Fig. 1.

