**Fig. 1. f1:**
[figure not shown]
Overview of timing of screening, intervention and assessments. Primary outcomes are assessed at baseline and week 13. Created in Biorender.com

Screening (telephone followed by in-person) and baseline (pre-intervention) assessments will be completed within 6 weeks prior to commencing the trial. The intervention duration lasts 12 weeks. Post-intervention testing will be performed in the week following the intervention. In groups involving PD, participants will be required to consume PPF supplements and in groups involving PA to complete home-based walking up to and including the day prior to returning for the final outcome assessment, respectively.

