### Randomisation, blinding and study allocation

Participants will be randomised upon meeting all eligibility criteria on completion of in-person screening and will be informed of their allocated group after baseline data have been collected. Randomisation will be stratified by study centre and sex. If a participant is identified as ineligible after randomisation and prior to baseline assessment due to error in screening^(53)^, a participant of the same sex will be randomised to the group the ineligible participant was allocated to. If members of the same household are eligible, they will be stratified to the same group. Randomisation will be centralised and conducted by an independent researcher, not connected to the project, using the QMINIM platform (Telethon Kids Institute, Australia). For the duration of the intervention and post-intervention assessments, both participants and researchers are unblinded to intervention allocation.

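### The random-coefficients label on the primary model does not fit two values per participant; reconcile it with the listed random effects, preferably as baseline-adjusted ANCOVA with centre and sex fixed

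*Protocol article*

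**What the plan says.** In the protocol article, the section on data management and statistical analysis sets the intention-to-treat analysis as one "using a random coefficients generalised linear mixed model for primary and secondary end points". For the fixed part it lists "The effects of time, the two interventions and their interaction", together with sex. For the random part it states: "Participant ID and study site will be included as random effects". It names no random slope, for time or for treatment, at either level.

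The design gives two occasions. Study design says that "outcome measures will be assessed pre and post a 12-week intervention", and the caption of Fig. 1 says "Primary outcomes are assessed at baseline and week 13". The primary outcomes section makes each endpoint one number per occasion: a "postprandial composite appetite score (area under the curve from 0 to 180 min") and the energy intake "from an *ad libitum* lunch test meal". There are three centres, and the randomisation section says: "Randomisation will be stratified by study centre and sex".

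**The concern.** In ordinary usage a random-coefficients model lets both the intercept and the slope vary by unit. With one value before and one after the intervention, a participant slope cannot be separated from residual error. The article therefore names a model class that its design does not support, and then lists random effects that suggest a simpler model. A statistician working from this text has to decide which was meant.

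A second, smaller point concerns centre. It was used to stratify the randomisation and has three levels, yet it enters as a random effect. Sex, the other stratification factor, enters as a fixed effect. No reason is given for treating them differently, and three levels say very little about a between-centre variance.

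What is at stake is a clear primary analysis and some precision. The validity of the treatment effect is not at stake.

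**Working it through.** **The plan's own figure.** The sample size section gives 180 participants (45 per group) for a 10 mm VAS difference, an SD of change of about 13 mm, 80% power and P < 0.05, with 20–25% dropout. Assume a two-sided test of two groups and apply the 10% allowance to the SD: 13 × 1.1 = 14.3 mm. Then n = 2 × (1.960 + 0.842)² × (14.3/10)² = 32.1, so 33 per group (34 by the t-test version). At 25% dropout, 33/0.75 = 44 per group gives 176, and 34/0.75 = 45.3, rounded up to 46, gives 184. The stated 180 lies between these. It rests on the SD of change, so nothing below alters it.

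**Identifiability.** Code the visits 0 and 1. Let the intercept variance be a, the slope variance b, their covariance c and the residual variance s. The model implies:

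- Var(baseline) = a + s
- Cov(baseline, week 13) = a + c
- Var(week 13) = a + 2c + b + s

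That is four unknowns in three equations. For any d that keeps the variances admissible, replacing (a, b, c, s) by (a + d, b + 2d, c − d, s − d) leaves all three quantities unchanged. The variance of the change, b + 2s, is also unchanged.

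One simulated two-visit dataset (assumed participant SD 170 kcal, residual SD 101 kcal) was fitted eight times by REML from different starting values and optimisers. The log-likelihood was −1657.09 each time. Three of the fits:

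| Fit | s | a | b | a + s | b + 2s |
|---|---|---|---|---|---|
| Highest s | 9,035.2 | 21,569.2 | 1,432.5 | 30,604.4 | 19,502.9 |
| Middle | 7,879.6 | 22,725.3 | 3,743.4 | 30,604.9 | 19,502.6 |
| Lowest s | 377.7 | 30,227.1 | 18,747.1 | 30,604.8 | 19,502.5 |

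The split is arbitrary, but the sums that carry the inference are fixed. The time-by-diet effect was 91.09 with SE 34.37 to 34.38 in all eight fits. A participant random-intercept model gave 91.09 with SE 34.38. That simpler model has two covariance parameters and both are identified. An uncorrelated intercept and slope would be just identified (three parameters, three elements).

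**Centre as random or fixed.** A variance estimated on 2 degrees of freedom has a 95% interval from 2/7.378 = 0.27 to 2/0.0506 = 39.5 times the estimate. In a simulation (assumed n = 132, site SD 60 kcal, residual SD 157.3 kcal), the site variance estimate had 5th and 95th percentiles of about 0 and 10,700 for a true value of 60² = 3,600. It was near zero in about 10% of runs. The treatment contrast hardly noticed:

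| Data | SE, centre fixed | SE, centre random intercept | Difference in estimate |
|---|---|---|---|
| Balanced | 38.38 kcal | 38.37 kcal | about 0 |
| About 15% missing | 41.77 kcal | 41.73 kcal | mean absolute 0.8, maximum 3.4 kcal |

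The planned difference is 120 kcal.

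**Gain from baseline adjustment.** Take the same variance v at both visits and correlation ρ. A contrast of changes has variance proportional to 2v(1 − ρ); ANCOVA has variance proportional to v(1 − ρ²). The SE ratio is √[(1 − ρ²)/(2(1 − ρ))] = √[(1 + ρ)/2]. The documents give no ρ, so a range is assumed:

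- ρ = 0.3: √0.65 = 0.81
- ρ = 0.5: √0.75 = 0.87
- ρ = 0.8: √0.90 = 0.95

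**The case against.** The strongest reply is that the article lists its random effects, and the list contains no slope. Read that way, participant and site are random intercepts and the model can be fitted to two visits; only the label is loose. Even on the worst participant-level reading, the treatment estimate and its standard error survive. Centre is in the model, so stratification is respected, and a poorly estimated centre variance is a nuisance quantity. A condensed article may also leave the covariance structure to a fuller plan. All of this stands, and it confines the point to one of specification. It does not remove the point, because the article positively names a model class that does not match its own list or its visit schedule.

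Three stronger readings are tempting, and the documents support none of them:

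- **The model will fail to converge, so a replacement will be picked after the data are seen.** Some software may refuse or warn, but failure is not certain. The treatment estimate does not depend on how the variance is split, and the Discussion says a blinded researcher will analyse the data.
- **Power collapses.** A critical t of 4.30 on 2 degrees of freedom, and about 35% power for a contrast designed at 80%, belong to a model with treatment effects varying randomly by centre. The article never states such a model.
- **The treatment effect cannot be estimated.** Non-identification concerns the separate variance components only.

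**Conclusion.** The point holds as a mismatch of specification. A participant random intercept with a correlated time slope and a residual is not identified from two values per person, so the label should go or be reconciled with the listed random effects. Random centre beside fixed sex is inconsistent but has negligible effect on the treatment standard error under the simulated values. The sample size does not change.

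The main practical gain lies in the replacement: ANCOVA lowers the standard error by about 5% to 19% against a contrast of changes. This assumes equal variances at the two visits, a pre-post correlation between 0.8 and 0.3, and that the planned two-visit model would estimate treatment as a difference in change with baseline group means left free.

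**What to change.** Delete the random-coefficients label. Analyse the week-13 value by ANCOVA with the baseline value, the two interventions and their interaction, and centre (two indicators) and sex as fixed effects. An equivalent choice is a two-visit model with an unstructured 2 × 2 covariance and a common baseline mean across groups, again with centre and sex fixed. Centre drops out for outcomes measured at one centre only.

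State how participants without a baseline value are handled, because plain ANCOVA omits them.

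The cost is analysis wording only: no new data, visits or participants. If a fuller analysis plan already writes the model out, it is enough to bring the article's wording into line with it and to say which governs.
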